formulated by Karachi University (chemistry department laboratories) for 20-30 seconds, thrice daily for 6 days. Group D (n=10) patients will use 2% hypertonic saline (Plabottle® by Otsuka Inc.) gargle and nasal lavage for a similar time period. Group E (n=10) will serve as positive controls. These will be given simple distilled water gargles and nasal lavage for 20-30 seconds, thrice daily for six days. For nasal lavage, a special douche syringe will be provided to each participant. Its use will be thoroughly explained by the data collection officer. After each use, patient is not supposed to eat, drink or mouth rinse for next 30 minutes.

**Discontinuation of intervention {11b}:** Patients who develop rashes, or any other mucosal reaction in oral mucosa or patients who do not wish to continue with the gargles and nasal lavage will be discontinued in the study.

**Compliance on intervention {11c}:** The data collection officer will monitor the amount of gargling solution consumed on daily basis to record the patient compliance on intervention. And once the study is over, the residual bottle will be collected and sent to the incineration. Similarly, any unused/ partially used study drug bottle will be destroyed via incineration.

**Concomitant care {11d}:** Study participants will continue to get their needed routine inpatient medical/pulmonology care concomitantly as per the individual requirements under the care of the attending physician(s).

**Outcomes {12}:** Primary outcome is the reduction in the intra-oral viral load confirmed with real time PCR. Secondary outcome is the change in inflammatory biomarkers (IL-2, IL-4, IL-6, IL-10, TNF- $\alpha$ , IFN- $\gamma$  and IL-17) profiles in the five study groups.

**Participants' timeline {13}:** The timeline has been added as a flow diagram at the end of the protocol. Please see figure 1 on page no. 15.

**Sample Size {14}:** As there is no prior work on this research question, so no assumptions for the sample size calculation could be made. The present study will serve as a pilot trial. We intend to study 50 patients in five study groups. For details, please refer to figure 1 on page no. 15.

**Recruitment {15}:** Patients who are laboratory confirmed COVID-19 within 7 days of the onset of their symptoms who are already admitted as inpatient at the Aga Khan University Hospital, Karachi, Pakistan will be contacted for a voluntarily participation in the study.

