**Group allocation/ Randomization {16a}:** The assignment to the study group/ allocation will be done using sealed envelope method under the supervision of Clinical Trial Unit (CTU) of Aga Khan University, Karachi, Pakistan. The patients will be randomized to their respective study group immediately after the eligibility assessment and consent administration is done.

**Allocation concealment {16b}:** All the study drugs will be kept in identical dark colored bottles so that the intervention is masked.

**Implementation {16c}:** The Neem extract (*Azadirachta indica*) will be compounded at the Chemistry department, University of Karachi, Pakistan. This will be arranged from there whereas other drugs are stored at AKUH pharmacy/ distribution department. The CTU will ensure that only labels mentioning A, B, C, D or E are pasted on the bottles.

**Blinding/ masking {17a}:** Study will be blinded in quadruple. Patients, intervention provider, outcome assessor and the data collection officer will be blinded. The groups will be labelled as A, B, C, D or E. The codes of the intervention will be kept in lock & key at the CTU and will only be revealed at the end of study or if the study is terminated prematurely.

**Un-blinding {17b}:** Although, un-blinding is not permissible, however, if a participant recognizes the intervention using his/her prior knowledge or experience; they will still be encouraged to continue with the study drug till the end of the study. But if any patients develops a serious reaction to the intervention drug, then un-blinding will be done. The principal investigator will consult CTU and with their permission and taking primary attending physician onboard, un-blinding for the patient in question will be done. This will be documented on the proforma.

**Specimen collection {18a}:** The baseline oral swab will obtained (by a trained data collection officer using the required PPEs) from the posterior pharyngeal wall/ tonsillar area of the study participant on day one before initiating the gargles. Study participants will continue to use the

gargle and nasal lavage for 6 days. The end-point oral-pharyngeal swab will be taken on the day 7. Participants will be provided with a protective hood so that they themselves don't generate aerosols in the immediate vicinity while carrying out the gargling and nasal lavage. For nasal lavage, they will use the special douche syringe as described earlier.

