**Retention of study participants {18b}:** To retain maximum number of patients in the study, the data collection officer will keep the contact number of all the recruited patients, so that even if they are discharged from the hospital, they will be encouraged to continue with the study protocol and present to us on the day 7 at the AKUH dedicated COVID-19 testing facility for the collection of their endpoint pharyngeal swabs.

**Data management {19}:** A trained data collection officer will be responsible for data entry, coding, security, and storage. To ensure data quality, double data entry will be followed. The data collection officer will ensure coordination with the investigators and the statistician.

The period of retention of the data will be according to the CTU policy on this subject i.e. 15 years after the completion of the trial. The biological samples (pharyngeal swabs), and the partially consumed study drug will be discarded via incineration immediately after the data collection.

**Data Analysis {20}:** Data will be analyzed using SPSS for Windows (version 23.0 SPSS) and Graph Pad Prism 7.0 software.

Mean and standard deviation of the continuous variables (age, COVID-19 viral counts and cytokine profiles at baseline and endpoint etc.) will be computed. Frequency distribution of the categorical variables will be determined (gender, co-morbidities, presence of hypertension, diabetes, periodontal status etc.) Repeated measures ANOVA will be used to compare the reduction in intra-oral viral load and the changes in the inflammatory biomarkers in the study groups. In case of substantially low count of participants in the study groups, non-parametric tests such as Kruskal-Wallis or Friedman test will be employed. Generalized Estimation Equation (GEE) will be done to predict changes in the COVID-19 viral load and cytokine profiles. A subset analysis using Zero inflated negative binomial (ZINB) model will be employed, provided a

significant reduction in viral load is observed in any of the study groups. A p-value of  $<0.05$  will be taken as statistically significant. {20a}

The **biases and confounders** can be taken care at following four levels:

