At recruitment stage, we will use restriction i.e. only those COVID-19 positive subjects will be recruited who have no other major co-morbidities. At intervention assignment, the random group allocation will ensure even distribution of the confounders in the study groups, thus their differential effect on the outcome will be taken care of. At analysis stage, we will employ GEE regression analysis (as described above) to account for biases and confounders and lastly, the subset analysis will stratify the data and nullify the effect of biases.

Interim analysis {20b} is not planned on account of a short duration of the study. Intention to treat analysis (ITT) will be adopted for missing data and protocol violations or deviations by uncompliant patients. {20c}

**Data monitoring {21a}:** It will be done bimonthly at two levels. The data monitoring committee comprising of principal and co-investigators will be responsible for the monitoring the data at the primary level whereas the CTU at the university level will oversee and monitor the overall conduct of the study.

The decision of termination of the study {21b} will be made in consultation with the director CTU and the sponsors/ funding agency. The decision will be made after mutual consensus of the parties.

**Harms/ adverse reaction reporting {22}:** The adverse events will be documented for each patient and will be reported bimonthly to the clinical trial unit (CTU). This will also documented in the final report. Sponsor/ funders will be notified of the adverse event using their case report. Due to topical nature of the intervention, most likely harm would be an allergic reaction to any of the study drugs [Povidone-Iodine, Hydrogen Peroxide or Neem Extract (*Azadirachta indica*)]. In case of any serious harm, the advice of the primary attending physician will take precedence over others. However, such patient will be discontinued in the trial, CTU and sponsors informed and un-blinding will be followed as prescribed in section 17b. The role of patient's medical insurance will be decided on individual basis

**Study Audit {23}:** CTU reserves the right of carrying out study audit by internal or external auditors anytime.

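### Sections 11b and 22 tie stopping the gargle to leaving the study, which undermines the intention-to-treat analysis promised in 20c because the only post-baseline swab may then not be taken

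*Protocol*

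**What the plan says.** Section 11b (Discontinuation of intervention) names two groups. The first is "Patients who develop rashes, or any other mucosal reaction in oral mucosa". The second is those who no longer want the solution: "patients who do not wish to continue with the gargles and nasal lavage will be discontinued in the study". The section heading speaks of the intervention; the sentence under it speaks of the study.

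Section 22 (Harms) returns to the matter for serious harm only: "such patient will be discontinued in the trial, CTU and sponsors informed".

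Section 20c (Data Analysis) states: "Intention to treat analysis (ITT) will be adopted for missing data and protocol violations or deviations by uncompliant patients".

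The primary outcome in section 12 is the reduction in intra-oral viral load. Section 18a provides a baseline swab on day 1 and one later measurement: "The end-point oral-pharyngeal swab will be taken on the day 7". Section 18b (Retention) keeps the contact numbers of all recruited patients so that "even if they are discharged from the hospital, they will be encouraged to continue with the study protocol" and return on day 7. The reason it gives is hospital discharge, not stopping the gargle.

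**The concern.** Two sections remove a patient who stops, and a third promises to analyse that patient. Whether the day-7 swab is taken is a matter of conduct that the protocol itself fixes. If it is not taken, no later analysis plan can recover it; it can only model the gap under assumptions that the data cannot test.

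The reasons for removal, a reaction to the solution or unwillingness to go on with it, are related to treatment, so the missing outcomes cannot be presumed random. With 10 patients per arm, each lost outcome is 10% of the arm.

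Section 20c adds a conceptual slip. ITT defines which patients are analysed and in which arm. It does not supply an outcome that was never measured.

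**Working it through.** **1. What the text requires when a patient stops the solution on, say, day 3**

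| Section | Consequence for the patient |
|---|---|
| 11b | Heading: intervention stops. Sentence: discontinued in the study |
| 22 (serious harm only) | Discontinued in the trial |
| 18a | Swab on day 7; silent on patients who have stopped |
| 18b | Recall on day 7, for discharged patients who carry on with the protocol |
| 20c | Analysed under ITT, non-compliance notwithstanding |

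No section says that the swab is still sought. The operative words of 11b and 22 point to removal, and 20c needs the outcome.

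**2. What the named methods do with such a patient**

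- Repeated measures ANOVA on two time points needs both values, so the patient is dropped. The same holds for Kruskal-Wallis applied to change.
- GEE keeps the baseline value, but there is no second post-baseline visit to carry information on the response. Standard GEE also assumes that missingness is unrelated to the unobserved outcome, which is doubtful when the cause is a reaction to the solution.

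**3. Where reactions are expected**

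Section 22 calls an allergic reaction the likeliest harm and lists povidone-iodine, hydrogen peroxide and Neem. Hypertonic saline and water are not in that list. No rate is given for any arm, so unequal loss is plausible but not documented.

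**4. Illustrative size**

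The plan has no effect size, SD, power or dropout figure to reproduce. Its only arithmetic is 5 groups × 10 = 50, which is consistent. The loss rates *d*, the gaps *g* and the 80% power below are my assumptions.

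- Chance that an arm of 10 loses at least one outcome: 1 − (1 − *d*)^10.
- Difference detectable with 80% power, two-sided 0.05, one depleted arm against a full arm of 10, normal approximation: (1.960 + 0.842) × √(1/n + 1/10) SD, with n = 10(1 − *d*).
- Shift of the completers' mean. If those lost would have had a reduction smaller by *g*, the full-arm mean is (1 − *d*)C + *d*(C − *g*) = C − *dg*. The completers' mean C therefore overstates it by *d* × *g*.

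| Assumed loss *d* | Outcomes left | P(at least one lost) | Detectable difference | Shift, *g* = 1 to 2 log10 |
|---|---|---|---|---|
| 0 | 10 | 0 | 1.25 SD | 0 |
| 10% | 9 | 65% | 1.29 SD | 0.1–0.2 log10 |
| 20% | 8 | 89% | 1.33 SD | 0.2–0.4 log10 |
| 30% | 7 | 97% | 1.38 SD | 0.3–0.6 log10 |

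At 20% loss the shift is a factor of 10^0.2 = 1.6 to 10^0.4 = 2.5 in copy number. Between two arms the error is *d*₁*g*₁ − *d*₂*g*₂. It is zero if loss and gap are equal in both arms, zero if *g* = 0, and reversed in sign if those lost would have done better. On a standardised scale, 20% loss with *g* = 0.5 to 1.0 SD gives 0.10 to 0.20 SD.

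**The case against.** **The text may mean only that the solution stops.** The 11b heading names the intervention, the day-7 swab is not made conditional on gargling, and contact numbers are kept for everyone. This stands in part: the wording is ambiguous and nothing says outright that the swab is dropped. But the sentence says study, section 22 says trial (though only for serious harm), and staff at the bedside would have to guess.

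**A reader might infer that ITT becomes impossible.** The documents do not support that. Patients can be analysed as randomised with a missing-data method, and that method may sit in an analysis plan not shown here. Undermined is the right word.

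**A reader might call the whole analysis completers-only.** That overlooks the planned GEE, which uses the available observations. GEE does not cure treatment-related loss with a single follow-up visit, but it is part of the plan.

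**A reader might take it as settled that irritant arms lose patients while the water arm stays complete.** No arm is described as irritant. The eligibility criteria exclude patients allergic to the study drugs and those with known chronic mucosal lesions, and the Rationale expects no significant adverse effects from Neem. Patients on water have the same thrice-daily gargle and lavage and may also refuse to go on.

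**The bias may be small beside the imprecision.** A shift of 0.10–0.20 SD is well below the 1.25 SD detectable with 10 per arm, and the trial is declared a pilot. This is fair as to size. It is no reason to lose outcomes that could be collected.

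**Conclusion.** The point holds as an inconsistency between 11b and 22 on one side and 20c on the other, with a direct effect on the primary outcome. Followed as written, patients who react or decline to continue have no day-7 value, for reasons related to treatment, and the loss cannot be undone afterwards. The use of ITT as a remedy for missing data is a misstatement in its own right.

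Direction and size of any bias are not established. The 0.2–0.4 log10 shift rests on three assumptions: 20% loss in one arm, a 1–2 log10 smaller reduction in those lost, and no offsetting loss in the comparator. The protocol's list of likely allergens makes unequal loss plausible and goes no further.

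**What to change.** - Reconcile 11b and 22 with 20c by treating stopping the solution and leaving the study as separate events. The rules for when treatment stops are not touched.
- State that the day-7 swab is sought from every randomised patient who has not withdrawn consent for it, and extend the 18b recall route explicitly to those who have stopped the solution.
- Reword 20c so that ITT means that all randomised patients are analysed in their allocated arm, and remove it as a method for missing values.
- Report missing day-7 outcomes and their reasons by arm. The choice of imputation or tipping-point method can be left to the SAP.

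The cost is a few sentences of protocol wording and a few extra follow-up contacts. The swabs are already planned for all 50 patients, and the protocol states that the grant pays for the PCR and cytokine tests.

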## **MATERIALS & METHODS:**

**Trial design {8}:** It will be a parallel group, quadruple blind-randomized controlled pilot trial annexed with a laboratory based study.

**Study settings & duration {9}:** The clinical trial will be carried out at the Aga Khan University Hospital (AKUH), Karachi, Pakistan. The total duration of the study is expected to be 6 months i.e. August 2020-January 2021. The viral PCR tests will be done at main AKUH clinical laboratories whereas the immunological tests (cytokine analysis) will be done at the Juma research laboratory of AKUH. The study protocol is already registered at [www.clinicaltrials.gov](http://www.clinicaltrials.gov) with ID# NCT 04341688.

**Sampling technique & Eligibility criteria {10}:** Non probability, purposive sampling technique will be followed to identify a total of 50 participants for this study. The inclusion criteria are laboratory confirmed COVID-19 positive males or females (in the age range of 18-65 years), with mild to moderate disease, already admitted in the AKUH. Subjects who have more than 7 days of the onset of COVID-19 symptoms, edentulous patients, subjects with low Glasgow coma score, intubated patients, history of radiotherapy or chemotherapy will be excluded. Patients who are being treated with any form of oral or parenteral antiviral therapy will be excluded. Patients with known pre-existing chronic mucosal lesions such as lichen planus will also be excluded. Patients who are allergic to the study drugs (Povidone-Iodine, Hydrogen Peroxide, Neem Extract or Hypertonic Saline) will also be excluded.

**Intervention {11a}:** Group A (n=10) patients on 10 ml gargle and nasal lavage using 0.2% Povidone-Iodine (Betadiene® by Aviro Health Inc./ Pyodine® by Brooks Pharma Inc.) for 20-30 seconds, thrice daily for 6 days. Group B (n=10) patients will be subjected to 10 ml gargle and nasal lavage using 1% Hydrogen peroxide (HP® by Karachi Chemicals Products Inc./ ActiveOxy® by Boumatic Inc.) for 20-30 seconds, thrice daily for 6 days. Group C will comprised of (n=10) subjects on 10ml gargle and nasal lavage using Neem extract solution (*Azardirachta indica*)

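### The concealment item {16b} describes product masking only, and five shared bottle letters with arms fixed at 10 make later assignments partly predictable and let one recognised bottle decode a whole arm

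*Protocol*

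**What the plan says.** All places are in the Protocol, Materials & Methods.

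- **Concealment {16b}.** The whole item reads: "All the study drugs will be kept in identical dark colored bottles so that the intervention is masked".
- **Randomization {16a}.** The "allocation will be done using sealed envelope method under the supervision of Clinical Trial Unit (CTU"). On timing: "The patients will be randomized to their respective study group immediately after the eligibility assessment and consent administration is done". The type of list, any block size, the envelope safeguards and who holds the envelopes are not described.
- **Labels {16c}.** "The CTU will ensure that only labels mentioning A, B, C, D or E are pasted on the bottles". Item {17a} repeats that the groups are labelled A to E.
- **Codes {17a}.** "The codes of the intervention will be kept in lock & key at the CTU".
- **Arms {11a}.** Each lettered group is tied to an agent and a size of 10: A povidone-iodine, B hydrogen peroxide, C Neem extract, D hypertonic saline, E distilled water. For example: "Group E (n=10) will serve as positive controls".
- **Sampling {10}.** "Non probability, purposive sampling technique will be followed to identify a total of 50 participants for this study".
- **Un-blinding {17b}.** The protocol anticipates that a participant may recognise the agent from prior knowledge or experience.

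**The concern.** Concealment and masking are different safeguards. Concealment hides the next assignment until the patient is irrevocably in the trial. Masking hides the product afterwards. Item {16b} answers the first question with the second.

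The envelopes in {16a} do address concealment, but the labelling rule works against them. When a group's letter is on every bottle and each letter is used exactly 10 times, a running tally of letters tells staff something about what remains. That information acts before enrolment, on who enters which group.

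The letters may also carry meaning. If the bottle labels follow the A-E listing in {11a}, locking the codes at the CTU protects little. If they do not, one recognised agent still reveals the content of every bottle with that letter.

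At stake is the comparability of the arms. The protocol's section on biases and confounders names random allocation as one of four controls and expects it to spread confounders evenly. With 10 per arm, two steered patients are 2/10 = 20% of an arm. Blinded PCR cannot repair an imbalance created at entry.

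**Working it through.** **Inputs.** Five groups of 10 ({11a}); 50 patients in total ({10}, {14}); one of five shared letters on each bottle ({16c}, {17a}). The list type is not stated.

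**1. Plan's own figure.** 5 × 10 = 50, which agrees with {14}.

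**2. Does 10 per arm imply a restricted list?** Under simple randomization, P(exactly 10 in each of five arms) = 50! / (10!)^5 / 5^50 = 0.0005. Fixed arms of 10 therefore imply a restricted list or a forced count.

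**3. Predictability with one list of 50.** The guesser has seen all earlier letters and names the letter with most places left. The chance of being right at each step is (largest number remaining) / (total remaining). Averaged over simulated random orderings of 10 of each letter:

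| Patients | Best guess correct |
|---|---|
| Chance level | 20% |
| All 50 | 30.8% |
| Last 10 | 49.2% |
| Last 5 | 60% |
| Patient 50 | 100% |

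In correct guesses:

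- All 50: 50 × 0.308 = 15.4, against 50 × 0.20 = 10 by chance.
- Last 10: 10 × 0.492 = 4.9.
- First 40: 15.4 − 4.9 = 10.5, and 10.5 / 40 = 26%.

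On average about 1.2 assignments per list are certain, and for about 9 assignments at least one letter is already used up. At least one letter is exhausted before patient 41 in 38% of lists and before patient 46 in 95%. An exhausted letter rules out one arm; it does not reveal the next one.

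**4. Sensitivity to block size (assumed; none is stated).**

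| Block size | Correct of 50 | Share | Certain assignments |
|---|---|---|---|
| 50 (single list) | 15.4 | 31% | 1.2 |
| 25 | 17.3 | 35% | 2.4 |
| 10 | 20.4 | 41% | 5.6 |
| 5 | 22.8 | 46% | 10 |

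Exact check for blocks of 5: 10 × (1 + 1/2 + 1/3 + 1/4 + 1/5) = 22.83.

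**5. Decoding.** With one letter per arm, one recognised bottle identifies the agent for 10 of 50 patients. With a unique number per bottle, it identifies 1 of 50.

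**The case against.** The strongest reply is that the protocol has a concealment step: sealed envelopes, CTU supervision, and randomization only after eligibility and consent. On that view {16b} is largely text under the wrong heading. This stands in part, and it limits the finding.

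Four stronger readings are tempting, and the documents do not support them.

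- **Allocation is effectively open at the level of the letters.** It is not. Under a single list the best guesser is wrong about 69% of the time overall, and over the first 40 patients gains about six percentage points on chance.
- **Every fifth assignment is certain.** That needs fixed blocks of 5, and no block size is stated.
- **Recruiters hand-pick patients while watching the letters.** Item {15} names nobody who contacts patients. The data collection officer explains the study at consent ({26a}) and checks solution use daily ({11c}). That this officer also selects patients or sees all earlier letters is an inference. Purposive sampling is also followed by fixed eligibility criteria.
- **The arms will be biased by a known amount.** The simulation measures guessing, not bias in viral-load change. The outcome is a reduction from a pre-gargle baseline, and eligibility narrows symptom duration and severity, so there is less to steer on.

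It is also fair to say that steering towards an agent requires a belief about what a letter means, and the codes are locked. This reply is weakened by the A-E listing in {11a} and by the recognition anticipated in {17b}.

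**Conclusion.** The point holds as a design weakness. The concealment item contains a masking measure, and the stated labelling rule undercuts the envelopes that do the concealing. If one list of 50 is used and someone sees all earlier letters, best-guess success is about 31% against 20%. The gain is concentrated late: about 26% in the first 40 patients and 49% in the last 10. Small fixed blocks would raise it, but whether blocks are used is unknown.

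Arm-wide decoding does not depend on the list type. It needs only one recognised agent, or bottle labels that match {11a}; whether they match is not stated.

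This is an avoidable risk of selection bias, not evidence that enrolment was or will be steered. It should be corrected because each arm is small and the remedy is cheap.

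**What to change.** - **{16b}:** state that the CTU holds a computer-generated list and releases the next bottle only after the patient's eligibility and signed consent have been logged with it.
- **{16c} and {17a}:** replace the A-E bottle labels with unique participant numbers 01-50, and keep the number-to-group key only at the CTU. The sentence in {17a} that labels the groups A to E must change too, or the two items will conflict.
- **{17a}:** move the dark-bottle sentence here, since it describes masking.

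Arms of 10 can be kept. The cost is a wording change, relabelling the bottles, and one CTU log entry per patient before release; no extra patients are needed. The change removes tallying by letter and arm-wide decoding from one bottle. It does not remove all guessing: if individual agents are recognised, they can still be counted against 10 per arm.

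### The bottles carry only the arm letters A to E, and the protocol prints which solution each letter denotes, so blinding is not secured for staff who know the protocol and handle the bottles

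*Protocol*

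**What the plan says.** Five parts of the protocol's methods bear on this point.

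- **Intervention {11a}** ties each group letter to a solution. For example, "Group A (n=10) patients on 10 ml gargle and nasal lavage using 0.2% Povidone-Iodine" and "Group D (n=10) patients will use 2% hypertonic saline". B is hydrogen peroxide, C is neem extract and E is distilled water.
- **Implementation {16c}** fixes the label: "The CTU will ensure that only labels mentioning A, B, C, D or E are pasted on the bottles".
- **Blinding/ masking {17a}** lists four blinded roles: patients, intervention provider, outcome assessor and data collection officer. It gives the groups the letters A to E and adds: "The codes of the intervention will be kept in lock & key at the CTU". Disclosure is reserved for the end of the study or early termination.
- **Un-blinding {17b}** allows an exception for an individual: "But if any patients develops a serious reaction to the intervention drug, then un-blinding will be done". The principal investigator, the CTU and the attending physician are involved.
- **Allocation concealment {16b}** adds identical dark bottles.

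No section mentions kit numbers, participant-specific codes, or a key linking bottle letters to solutions that differs from the list in {11a}.

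**The concern.** A letter code blinds only while its key is secret. Here the locked key appears to be the list already printed in {11a}. Anyone who has read that section and sees a lettered bottle can name the solution.

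This matters most for the data collection officer, who is meant to be blinded but is in contact with both bottles and patients. Under Compliance {11c}, "The data collection officer will monitor the amount of gargling solution consumed on daily basis". The officer also:

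- teaches the nasal lavage ({11a});
- takes the baseline swab ({18a});
- keeps in touch with discharged patients so that they continue and come back on day 7 ({18b});
- is responsible for data entry and coding ({19});
- explains the study to patients at consent ({26}), and so can be expected to know its content.

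Recorded compliance, encouragement to continue, day-7 return and data handling are therefore all open to influence by known allocation. With 10 planned patients per arm, a few differential losses could matter. The blind is claimed in the trial's title and in the design statement, so the protocol should secure it.

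**Working it through.** There is no stated figure to reproduce. The check sets the passages side by side and then counts.

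**Step 1. Compare the printed letters with the bottle letters.**

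| Letter | Solution according to {11a} | Among the bottle letters in {16c}? |
|---|---|---|
| A | "Group A (n=10) patients on 10 ml gargle and nasal lavage using 0.2% Povidone-Iodine" | yes |
| B | "Group B (n=10) patients will be subjected to 10 ml gargle and nasal lavage using 1% Hydrogen peroxide" | yes |
| C | "Group C will comprised of (n=10) subjects on 10ml gargle and nasal lavage using Neem extract solution" | yes |
| D | "Group D (n=10) patients will use 2% hypertonic saline" | yes |
| E | distilled water | yes |

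All 5 letters match a named solution, and {16c} allows nothing else on the label.

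**Step 2. Ask whether bottle letter A must be Group A.** {17a} applies A to E to the groups, which is how {11a} uses them. That makes identity the natural reading. It is not stated outright, and the locked code in {17a} would have a purpose only if the CTU held something not already printed. The protocol leaves the matter unresolved.

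**Step 3. Count under each reading, using the planned 10 per group.**

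- *Letters coincide:* 5 × 10 = 50 of 50 allocations can be read from the bottle by someone who knows {11a}.
- *Letters scrambled by the CTU:* none can be read at the outset. Once one letter is linked to its solution, the whole arm is known: 10 of 50. The {17b} procedure, meant for a single patient, makes such a link. It cannot be confined to that patient because the other nine in the arm carry the same letter.

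**Step 4. Ask which of the four blinded roles the label reaches.**

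- *Intervention provider and data collection officer:* exposed if they know the protocol, because their work involves the bottles.
- *Patients:* they see the letter, but nothing shows that they are given the protocol.
- *Outcome assessors:* nothing says that swab tubes carry the arm letter. PCR results are read as Ct values against a standard curve ({33}).

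**Step 5. Ask who takes the swabs.** The officer is named only for the baseline swab, taken before gargling starts ({18a}). No operator is named for the day-7 swab, and discharged patients are sent to the hospital's dedicated testing facility ({18b}).

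**The case against.** The strongest reply is that the CTU's locked code must be a re-mapping of the letters, since locking away a list already printed in the protocol would be pointless. The text permits that reading, so it would be wrong to state as fact that no secret remains. But the protocol does not say it, and the use of the same letters for the groups in {17a} points the other way. A re-mapping would also leave the shared-letter weakness under {17b}.

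A reader might also infer that the blind fails for all four roles. The documents do not support that. The label informs only people who know {11a}, and neither patients nor laboratory assessors are shown to be exposed through it. A patient who recognises a solution by taste or colour is a separate matter, which {17b} foresees and which new labels would not cure.

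Nor can it be inferred that a knowing operator biases the day-7 swab. That operator is not named, and the protocol gives no figure for the effect of operator on swab yield.

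Finally, {17b} does not say that the officer is told the result of an un-blinding, so the arm is revealed only to those who learn it. That limit stands. It does include the principal investigator, who also sits on the data monitoring committee ({21a}).

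**Conclusion.** The point holds as a contradiction on the face of the protocol. {11a} publishes the meaning of the group letters, while {16c} and {17a} put those letters on the bottles and call the code locked. The quadruple-blind claim is therefore not secured for the intervention provider and the data collection officer.

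The size depends on the reading:

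- All 50 planned allocations are readable by protocol-aware bottle handlers if bottle letters equal group letters. This is the natural but unstated reading.
- If the letters are scrambled, 10 of 50 are disclosed for each letter that becomes known.

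Both counts assume the planned 10 per group. They measure exposure, not bias in viral load, and the documents give no basis for estimating such a bias. The instrument-read PCR and cytokine outcomes limit the room for assessor bias. They do not protect compliance recording, retention or data handling. The defect should be corrected before bottles are labelled, because a lost blind cannot be restored at analysis.

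**What to change.** Amend {16c}, {17a} and {17b} as follows:

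- Replace the arm letters on the bottles with unique participant or kit numbers issued from the CTU randomisation list.
- State that these numbers bear no relation to the group letters in {11a}, and that only the CTU holds the key.
- Identify swabs and laboratory samples by that number alone.
- Have any {17b} un-blinding open a single kit number, so that it discloses one patient and not an arm.

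The cost is relabelling, a CTU kit list and a short amendment to the three sections. No extra patients or visits are needed. Kit numbers will not hide taste or colour, but they close the label route and keep each disclosure to one patient.
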